**Participant recruitment:**

**a)Mapping of organisations dealing with children with CP within the Iganga, Mayuge and Bugweri districts as catchment areas.**

Implementing health and research organizations with specialty in community based research and rehabilitation of childhood disabilities including CP, and operating within the study catchment area will be identified and approached for participant identification with the help of community leaders and other key informants. Currently, three organizations dealing with children with CP are known to operate in the study area, and these include: i) the CURIE research project that identified and followed up 97 children with CP within the IMHDSS (described in sub-study 1) in 2015[^9^](#_ENREF_9) to 2019, ii) the Musana Community Health Center (MCHC) a 24-hour facility operating in Iganga district since February 2016 ([www.musana.org](http://www.musana.org)), and EKISA ministries. The MCHC offers affordable services in pediatrics, occupational and physical therapy, minor surgeries, maternity, and community outreach programs within the most rural areas of Iganga. The MCHC also receives patients from neighboring districts including Bugiri, Mayuge and Bugweri.

1. **Identifying children with CP and their caregivers:**

Lists of all children with a confirmed diagnosis of CP will be compiled by a trained community mobiliser from databases of selected community based rehabilitation and research entities (CURIE) as well as additional case finding through community leaders, to make the required number from which to screen the study participants. These lists will include full names of the child and caregiver including contact details and home addresses. Children with missing caregiver contacts or home addresses will be omitted. Caregivers will be traced through phone contacts and household visits to confirm physical address, presence of the CP child and to eliminate participant duplication. Through home visits, voluntary consent for study participation will be sought from all caregivers of children with CP. Unique identification numbers will be assigned to consented caregivers and their children to be enrolled in the study.

1. **Screening for CP child malnutrition:**

To screen for malnutrition, CP child anthropometric measurements will be recorded by a trained clinical officer using standardized WHO protocols[^11^](#_ENREF_11). Standing height will be measured for children > 5 years and recumbent length will be taken for children <5 years, both measured to nearest 0.1cm. Knee height will be recorded for all children to the nearest 0.1cm using a flexible tape measure and used to determine an estimated body height for those who cannot stand, by using the Stevenson formula[^12^](#_ENREF_12). Weight will be measured and recorded to the nearest 0.1kg using a SECA 813 digital scale (seca Vogel & Halke GmbH &Co., Hamburg, Germany). Children who can’t stand independently will first be weighed together with their caregiver and then the weight of the caregiver alone subtracted to obtain the child’s weight. Following WHO best-practice procedures, mid Upper Arm Circumference (MUAC) for all children will be measured using a standard UNICEF MUAC tape.

**Defining malnutrition**:

Anthropometric indicators will be constructed according to WHO growth standards based on weight, height/length, age and sex[^11^](#_ENREF_11) and converted into Z-scores using the WHO Anthro[^13^](#_ENREF_13) and Anthro-Plus to calculate the nutritional status for children within the 2-19 years age range. For those older than 19 years, the LMS method will be used to determine their weight, height and body mass index (BMI) by age and sex standard deviation scores[^14^](#_ENREF_14). Children with a Z-score of < -2 SD in any of the nutritional indicators will be defined as having Malnutrition. Classifications for MUAC will be made by comparing the arithmetic mean of the two measurements (i.e. the “gold standard” measurement) against case defining thresholds for moderate acute malnutrition (MAM) i.e. for children, MUAC < 12.5 cm and severe acute malnutrition (SAM) MUAC < 11.5cm[^15^](#_ENREF_15)^,^ [^16^](#_ENREF_16). For adult (>18years) thresholds, MAM MUAC <23.0 cm and SAM MUAC <21.0cm[^17^](#_ENREF_17). The caregiver of a child or adolescent who is identified as MAM will be enrolled for the intervention study consecutively to make-up for the required study sample (124 caregivers). Caregivers of children or adolescents identified as serious SAM will be counselled about the life saving importance of early management of malnutrition and thereafter referred to the nearest treatment site based on ministry of health guidelines [^18^](#_ENREF_18). Anthropometric findings for those enrolled will be recorded as baseline for the intervention study.

**Outcome measures**

**Primary outcome**: Nutritional status: The primary outcome measure will be a weight gain of >200grams in 12 days[^10^](#_ENREF_10) and ≥ 900g within 3 months.

**Secondary outcomes** will include change in anthropometric Z scores for any of weight, height and BMI, and MUAC classification measure, and Caregiving. The caregiver outcome measure will include a score of the questionnaire evaluating caregiver’s basic nutrition and feeding knowledge before and after the intervention.

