**Sample size estimation:**

1. **Sample size estimation in a between subjects 2x2 factorial design (Bonnet,2016)**

**
[figure not shown]
**

In order to estimate a main effect in a between-subjects 2x2 factorial design at 95% confidence, at desired confidence interval width of 2.0, and a planning value of 8.0 for the average within group error variance, the contrast coefficients are 0.5, 0.5,-0.5 and-0.5, and the sample size required per group is approximately 31.

1. **Sample size estimation using two proportions:**

The PD program has been reported to increase weight of ≥200g in 12 days among 87% of participants in Burundi [^10^](#_ENREF_10). Based on the prevalence of malnutrition (<-2sd in any of HAZ,WAZ,BMIZ) among the CURIE CP population based cohort reported as 64% as per the 2015 assessments. Assuming the previously reported effect of the PD program, we hope to reduce malnutrition in the CP child population to about 29%, at α =0.05, and power (1-β) =0.8. After imputing these parameters into a Stata program to estimate sample size for individual randomization, of a two proportions test, the estimated total sample size is 62: Hence 31 participants per each of the four arms. Therefore for a 2x2 factorial trial, assuming a 1:1:1:1 allocation, 124 participants will be required for the study with 32 participants in each of the four conditions.

Participants in this study will include eligible caregivers of children with CP participating in the wider CURIE intervention study (Akwenda). In order to account for those that may not be malnourished from the CURIE study sample, additional caregivers of malnourished children with CP will be recruited from community-based organizations (CBOs) operating within the study setting including EKISA ministries and MUSANA community health centre. The CURIE intervention study has got two arms (PFT and Control) separated as village clusters based on geographical proximity and balanced by age, and GMFCS level. This study will utilize the available CURIE intervention clusters to avoid contamination. Details of participant recruitment from different CBOs are displayed below.

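### The primary outcome is defined by gram cut-offs although weight is recorded to 0.1 kg; analysed as defined, it discards the size of the gain, at a cost in power that depends on assumptions

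*Protocol*

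**What the plan says.** The Outcome measures section defines the primary outcome by two thresholds. The first is "The primary outcome measure will be a weight gain of >200grams in 12 days" and the second, joined to it by the word *and*, is "≥ 900g within 3 months". The secondary outcomes include change in weight, height and BMI Z scores. Change in weight in grams or kilograms is not listed as primary or secondary.

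The measurement itself is finer. The anthropometry text under Participant recruitment says: "Weight will be measured and recorded to the nearest 0.1kg using a SECA 813 digital scale".

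Two other parts of the protocol treat the outcome as a mean:

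- The first calculation under Sample size estimation uses a confidence interval width of 2.0 and "a planning value of 8.0 for the average within group error variance". It gives no unit and no source for the 8.0.
- Data management and analysis plans a two-way ANOVA and pairwise comparison of treatment means. It does not name the response variable.

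The second sample-size calculation does use proportions, but of malnutrition prevalence: 64% in the 2015 cohort, and "we hope to reduce malnutrition in the CP child population to about 29%, at α =0.05, and power (1-β) =0.8". The only rate given for the 200 g threshold is the programme figure: "The PD program has been reported to increase weight of ≥200g in 12 days among 87% of participants in Burundi".

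**The concern.** A responder definition keeps one bit of information per child. At three months, a child who gains 0.8 kg counts the same as one who loses 1 kg, and a child who gains 0.9 kg counts the same as one who gains 4 kg. The scale reading that separates these children is already taken.

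The protocol does not argue for the cut. The 200 g threshold rests on one cited programme study, the 900 g threshold has no citation, and no regulator or guideline is cited as requiring either. Neither sample-size calculation concerns a weight-gain responder rate.

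With the sample fixed at 124, information lost in the definition of the outcome is not recovered elsewhere. A real main effect of either factor would be more likely to be missed, and the interaction, which is estimated less precisely, would suffer too.

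**Working it through.** **Inputs.** Main-effect comparison of 62 v 62 (column totals of Table 1). Two-sided 5% (Data management and analysis). Variance 8.0, interval width 2.0, and 64% v 29% at 80% power (Sample size estimation). The protocol gives no comparison-level responder rate, so a range is shown.

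**Step 1: reproduce the plan's figures.**

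- Interval width, with contrast coefficients ±0.5 (sum of squares 1): n = 4 × 8.0 × 1 × (1.96/2)² = 30.7, so 31 per group, as stated. This is a formula for a mean. A 0/1 variable has variance of at most 0.5 × 0.5 = 0.25, so 8.0 cannot be the variance of a responder indicator.
- Two proportions, 64% v 29%, pooled variance, no continuity correction: 31 per group, 62 in total, as stated.

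**Step 2: cost of one cut in an illustrative model.** Assume normal gains, equal SD and a single threshold.

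- The effect with 80% power on the full scale at 62 v 62 is d = 0.507 SD (noncentral t). It is chosen to give 80%; the protocol does not state it.
- If a proportion p of the comparison level passes, the proportion passing in the other level is Φ(Φ⁻¹(p) + 0.507).
- Power is that of the two-proportion z-test at 62 v 62. Example at p = 40%: Φ(−0.253 + 0.507) = 60%. The null standard error is √(2 × 0.25/62) = 0.0898 and the alternative one is √((0.24 + 0.24)/62) = 0.0880. Power = Φ((0.200 − 1.96 × 0.0898)/0.0880) ≈ 61%.

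| Comparison level passing | Other level passing | Power as responder rate |
|---|---|---|
| 5% | 13% | 33% |
| 10% | 22% | 44% |
| 20% | 37% | 55% |
| 30% | 49% | 60% |
| 40% | 60% | 61% |
| 50% | 69% | 60% |
| 60% | 78% | 57% |
| 70% | 85% | 51% |
| 80% | 91% | 42% |
| 87% | 95% | 33% |

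Between 10% and 80% passing, the loss against 80% is 19 to 38 points. If the quoted 87% is instead the rate with PD, the comparison rate is 73% and power is 49%.

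Cross-check by relative efficiency: a cut at the median keeps 0.637 of the information, so power = Φ(2.80 × √0.637 − 1.96) ≈ 61%.

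**Step 3: the only effect the plan states.** 64% v 29% corresponds to a latent difference of 0.358 + 0.553 = 0.912 SD.

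| Comparison | As proportions | On the full scale |
|---|---|---|
| 31 v 31 | 80.4% | 94.2% |
| 62 v 62 | 98.1% | 99.9% |

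At the main-effect size of 62 v 62 the loss is under 2 points. The 64% v 29% is a difference in malnutrition prevalence, not in weight-gain responders.

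**Step 4: relax the equal SD.** Participants are aged 2-24 (Study population), so gains in kg may vary much more in some than in others. Illustrative simulation at 62 v 62, all inputs assumed: individual SD uniform from 0.4 to 2.0 kg, mean comparison gain 0.5 kg, cut at 0.9 kg.

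- Constant benefit of 0.65 kg: 80% power for the t-test, 83% for the responder rate.
- Benefit proportional to the individual's SD, sized to give the t-test 80%: about 68% for the responder rate.

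The loss under this model runs from none to about 12 points.

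**The case against.** The strongest objection is that the loss depends on a reading the protocol does not settle. The analysis section speaks of means and ANOVA throughout. If the ANOVA is run on weight change, nothing is lost. That is right, and it is why the point is conditional. But the Outcome measures section then misdescribes the primary outcome, and the same edit is needed.

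A reader might infer that this trial has only 42-61% power. The documents do not support that. The 0.507 SD effect is back-solved, the protocol states no such effect, and for the effect it does state the loss at 62 v 62 is under 2 points. The range is not a floor either, since more extreme passing rates go lower. It also describes one cut, whereas the protocol joins two and gives no joint rate.

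A reader might also infer that the variance-8.0 calculation would cover weight once weight is primary. That is unsupported while 8.0 has no unit or source.

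Two further objections stand in part. Continuous Z-score changes are kept as secondary outcomes, so the information is not lost to the trial as a whole, only to its primary result. And a threshold taken from a cited programme study is a legitimate endpoint that allows comparison with that study. This is a reason to keep the responder rates as supportive results. It does not require them to carry the primary test.

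**Conclusion.** The point holds in conditional form and should be acted on. The primary outcome is defined by cut-offs, while the first sample-size calculation and the ANOVA are for means. If it is analysed as defined, the size of the gain is discarded.

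With one cut, normal gains and equal SD, an effect with 80% power on the full scale falls to about 42-61% when 10-80% of the comparison level pass, and to about 33% at 5% or 87%. The loss is negligible for effects as large as 64% v 29% at 62 v 62, and it can be small or absent when the spread of gains differs greatly between participants. The size is therefore uncertain. The mismatch between the sections does not depend on these assumptions.

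**What to change.** Make month-3 weight in kg, or its change from baseline, the primary outcome on the full scale. Analyse it in the factorial model with baseline weight as a covariate, and age as well because the range is 2-24 years. The Outcome measures section then matches the planned ANOVA.

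Report the proportions gaining >200 g in 12 days and ≥900 g within 3 months as supportive secondary results.

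State the unit and source of the variance of 8.0 before applying that calculation to the new primary outcome.

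The cost is protocol wording. Baseline anthropometry, monthly growth monitoring of all children and the three-month assessment are already planned, so no visits or participants are added. The downside is that the 12-day component, and the responder rate comparable with the cited programme study, become secondary.

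### The secondary outcome takes MUAC as a class at the entry cut-offs, which discards more than half of its information at modest gains; MUAC in cm adjusted for baseline is the better measure

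*Protocol*

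**What the plan says.** The Outcome measures section names, among the secondary outcomes, "change in anthropometric Z scores for any of weight, height and BMI, and MUAC classification measure". It gives no direction, time point or minimum change for the MUAC part.

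The only MUAC classes are in Defining malnutrition. They are "for children, MUAC < 12.5 cm and severe acute malnutrition (SAM) MUAC < 11.5cm", and for those over 18 years "MAM MUAC <23.0 cm and SAM MUAC <21.0cm". The class is set by "comparing the arithmetic mean of the two measurements" with these thresholds.

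The same section ties entry to the same classes: "The caregiver of a child or adolescent who is identified as MAM will be enrolled for the intervention study consecutively". It then states: "Anthropometric findings for those enrolled will be recorded as baseline for the intervention study". So one set of cut-offs serves entry and outcome, and the reading that admits the child is also the baseline.

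Entry is not by MUAC alone. The section also says: "Children with a Z-score of < -2 SD in any of the nutritional indicators will be defined as having Malnutrition". The Study flow chart likewise lists Z-scores and MUAC together as inclusion criteria.

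The only inferential method in Data management and analysis is a two-way ANOVA with PD, PFT and their interaction, followed by pairwise comparison of means.

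**The concern.** A child enrolled on MUAC starts inside a band 1.0 cm wide (12.5 − 11.5), or 2.0 cm for an adult (23.0 − 21.0). Three things follow when the outcome is the class.

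- **Change inside the band is invisible.** From 11.6 to 12.4 cm is a gain of 0.8 cm and counts as no change. From 12.4 to 12.5 cm is a gain of 0.1 cm and counts as an improvement.
- **Some children cannot improve.** A child who enters on a Z-score with MUAC at or above the cut-off is already in the best class and can only stay or worsen.
- **Some children cross without real change.** Selection on a reading that is also the baseline brings regression to the mean. Averaging two readings reduces the error but leaves variation between visits and observers: a clinical officer screens, while independent or external assessors do later measurements.

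At stake is the chance of seeing a modest real effect on MUAC. In addition, a before-after proportion leaving the moderate class, if quoted for one arm alone, would be too favourable.

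**Working it through.** **The plan's own figure.** The protocol states no power for MUAC. Its two-proportion sample size reproduces: for 64% v 29%, two-sided α 0.05, power 0.80, n = [1.96·√(2·0.465·0.535) + 0.842·√(0.64·0.36 + 0.29·0.71)]² / 0.35² = (1.383 + 0.556)² / 0.1225 ≈ 30.7, so 31 per group. Table 1 puts 31 in each cell, so each main effect compares 62 with 62. That is the size used below.

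**Inputs.** From the protocol: the cut-offs, the mean of two readings, and 62 v 62. Assumed, because the protocol does not give them: the MUAC distribution, the error SD σ of the two-reading mean, the true gain, and the SD of individual growth.

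**1. Crossing with no true change** (observed entry 11.5 to <12.5 cm, one later reading of 12.5 cm or more). With a flat MUAC density the share is about σ·√2·0.399 / band width = 0.564·σ / width. A single-reading SD of 0.1 cm gives σ = 0.1/√2 = 0.07 and 0.564·0.07/1.0 = 4%. At σ = 0.2 it is 11%. Simulation results:

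| σ (cm) | flat density | N(14, 1.3) |
|---|---|---|
| 0.15 | 9% | 14% |
| 0.2 | 11% | 18% |
| 0.3 | 17% | 27% |
| 0.4 | 22% | 34% |

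The range is thus about 4% to 34%. In the wider adult band with flat density it is 4%, 6% and 10% for single-reading SD 0.2, 0.3 and 0.5 cm.

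**2. Power, 0.2 cm gain, growth SD 0.3 cm, all enrolled on MUAC.** For cm adjusted for baseline, the residual variance within so narrow a band is about growth² + 2σ².

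- σ = 0.2: √(0.09 + 0.08) = 0.412; SE = 0.412·√(2/62) = 0.074; 0.2/0.074 = 2.70; power = Φ(2.70 − 1.96) ≈ 77%.
- σ = 0.3: √(0.09 + 0.18) = 0.520; SE = 0.093; 0.2/0.093 = 2.14; power ≈ 57%.

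Simulation with N(14, 1.3) gives about 75% to 77% and 56% to 58% for cm. For the class (two-proportion test) it gives about 40% to 42% and 31% to 33%. Under no effect both methods reject about 5% of the time.

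**3. Information kept by the class.** Convert power to the expected test statistic, z = 1.96 + Φ⁻¹(power), and square the ratio.

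- σ = 0.2: 40% → 1.71, 75% → 2.63; (1.71/2.63)² ≈ 0.42.
- σ = 0.3: 31% → 1.46, 56% → 2.11; (1.46/2.11)² ≈ 0.48.

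More than half is lost in each case.

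**4. Noise or cut-off?** In another scenario (control gain 0.1 cm, treatment effect 0.3 cm, SD of true change 0.4 cm, flat density), class power is 70% with no measurement error at all, against 99% for cm. With single-reading SD 0.2, 0.3 and 0.5 cm the pairs are 65% v 96%, 59% v 92% and 45% v 74%. The cut-off itself is the larger loss.

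**5. Mixed entry.** Under the assumptions of step 2, with the remaining children drawn from 12.5 cm or more, class power falls to about 9% to 19% if a quarter to a half enter below the MUAC cut-off. Power for cm hardly moves.

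**6. Large effect.** With a uniform 0.5 cm gain and 62 v 62, class power stays at or above 95% even at single-reading SD 0.5 cm.

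**The case against.** The strongest reply is that the protocol writes no single-visit recovery rule. It names a classification measure and schedules repeated assessments; a responder definition for a secondary outcome may sit in a statistical analysis plan that is not shown. That stands: the missing confirmation rule is not the point here. What the protocol does fix is the class as the outcome and one set of cut-offs to form it. A later definition of change in class would still start from that scale.

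A reader might also infer that noise turns roughly one child in ten to one in three into a false recovery. The documents do not support that as a fact. They give no MUAC error or distribution, the low end is about 4%, and the high end needs both a large error and a density rising across the cut-off. Nor do they support reading noise as the main cause (step 4).

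A further tempting inference is that the PD or PFT comparison is biased. It is not on this account: crossings by noise occur in all four conditions, assessors are to be blinded, and type I error stays near 5%. The protocol does not plan to report uncontrolled recovery proportions.

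It is fair, too, that this is one secondary outcome, that Z-score changes for weight, height and BMI are already kept, that no power is claimed for MUAC, and that the two-proportion test is an assumed analysis. The share enrolled on MUAC is unknown. A smaller share, however, weakens the class further and leaves cm almost untouched.

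**Conclusion.** The point holds as a matter of outcome scale. Taking MUAC as a class at the entry cut-offs gives up more than half of its information for a modest effect: about 40% v 75% power at error SD 0.2 cm and 31% v 56% at 0.3 cm. Those figures assume a 0.2 cm gain, growth SD 0.3 cm, 62 v 62, MUAC distributed N(14, 1.3) and every child enrolled on MUAC. The loss is greater if many children enter on Z-scores, and negligible for a 0.5 cm gain. The between-arm test stays valid as far as measurement noise is concerned. The change is worth making because it costs little, but the primary outcome is not affected.

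**What to change.** In Outcome measures, name the outcome as MUAC in cm at 3 months (mean of the two readings) in place of the MUAC class. In Data management and analysis, analyse it with PD, PFT and PD×PFT terms plus baseline MUAC in cm. This extends the planned two-way ANOVA by one covariate and agrees with the limitations section, which already speaks of adjusting for baseline differences. Keep the MUAC class as a descriptive table by arm.

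The cost is wording only: MUAC is already measured for all children and growth monitoring is already monthly. The cm scale also avoids the jump in cut-off from 12.5 to 23.0 cm for a participant who passes 18 years during follow-up. The small downside is that a mean difference in cm is less directly readable than a change of class, which the table still shows.
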